#### **3.2 Ethical Conduct of the Study**

This study will be conducted in accordance with the ethical principles that have their origins in the Declaration of Helsinki, in compliance with the approved protocol, GCP and applicable regulatory requirements.

#### **3.3 Subject Information and Consent**

The investigator will obtain a freely given written consent or assent from each subject or parent or guardian after an appropriate explanation of the aims, methods, anticipated benefits, potential hazards, and any other aspects of the study that are relevant to the subject's decision to participate. The consent form must be signed and dated by the subject or parent or guardian before he/she is exposed to any protocol-specific procedure.

The investigator will explain that the subjects are completely free to refuse to enter the study or to withdraw from it at any time, without any consequences for their further care and without the need to justify.

The subject will receive a copy of the subject information and the signed informed consent.

The subject will be informed if information becomes available that may be relevant to his/her willingness to continue participation in the study.

Each subject will be informed that a monitor or a health authority inspector, in accordance with applicable regulatory requirements, may review the portions of their source records and source data related to the study. Data protection and confidentiality will be handled in compliance with local laws.

## 4 INTRODUCTION

Gaucher disease is a lipid storage disease characterized by the deposition of glucocerebroside in cells of the macrophage-monocyte system. The disorder results from the deficiency of a specific lysosomal hydrolase, glucocerebrosidase (also termed acid  $\beta$ -glucosidase, glucosylceramidase). The disease is characterized by a continuum of phenotypes. The severity widely varies; some patients present in childhood with virtually all the complications of Gaucher disease, whereas others remain asymptomatic into the eighth decade of life.

Glucosylceramide, the accumulated glycolipid, is primarily derived from the phagocytosis and degradation of senescent leukocytes and, to a lesser extent, from erythrocyte membranes. The glycolipid storage gives rise to the characteristic Gaucher cells, macrophages engorged with lipid with a crumpled-tissue-paper appearance and displaced nuclei.

Glucosylceramide accumulation in the bone marrow, liver, spleen, lungs, and other organs contributes to pancytopenia, massive hepatosplenomegaly, and, at times, diffuse infiltrative pulmonary disease. Progressive infiltration of Gaucher cells in the bone marrow may lead to thinning of the cortex, pathologic fractures, bone pain, bony infarcts, and osteopenia. These bony features may also be related to macrophage-produced cytokines.

Enzyme replacement therapy (ERT) for Gaucher disease is available, with most patients receiving recombinant enzyme (imiglucerase [Cerezyme®]). ERT is highly effective in reversing the visceral and hematologic manifestations of Gaucher disease.

ERT is indicated for patients with Gaucher disease who exhibit clinical signs and symptoms of the disease, including anemia, thrombocytopenia, skeletal disease, or visceromegaly. ERT is not effective in neuronopathic forms of the disease. Severity and rate of disease progression widely varies, especially in adults, which makes treatment decisions extremely difficult in some patients. Generally, subjects who present symptomatically, rather than because of family history, may have severe disease manifestations that require early treatment. Presymptomatic treatment with imiglucerase remains controversial because of the lack of prognostic correlation between genotype and disease severity and the high cost of the therapy.

Unmodified human glucocerebrosidase (hGCD), derived from natural sources, cannot be targeted to the phagocytic cells in the body and is, therefore, of limited therapeutic value. In developing the current therapeutic products for Gaucher disease, the terminal sugars on the carbohydrate chains of hGCD are sequentially removed by treatment with three different glycosidases. This glycosidase treatment results in a glycoprotein whose terminal sugars consist of mannose residues. This facilitates uptake by mannose receptors on phagocyte cells that recognize glycoproteins and glycopeptides with oligosaccharide chains that terminate in mannose residues. The carbohydrate remodeling of hGCD improves the targeting of the enzyme to these cells.

Since the glycosylation pattern of hGCD must be remodeled to generate high mannose structures to increase uptake in target cells, the expression of hGCD in plant cells could be of great value. Post-translational modifications do not exist in bacterial expression systems, but plant derived expression systems do facilitate these modifications known to be crucial for protein expression and activity. One of the major differences between mammalian and plant protein expression systems is the variation of protein sugar side chains, caused by the differences in biosynthetic pathways. Glycosylation has been shown to have a profound effect on activity, folding, stability, solubility, and susceptibility to proteases, blood clearance rate and antigenic potential of proteins. Hence, any protein production in plants should take into consideration the potential ramifications of plant glycosylation.

The production of taliglucerase alfa utilizes *Agrobacterium tumefaciens*, a bacterium capable of inserting single stranded DNA molecules into the plant genome. Due to the relative simplicity of introducing genes for mass production of proteins and peptides, this methodology is becoming increasingly popular as an alternative protein expression system.

The plant cell expressed recombinant hGCD (taliglucerase alfa) is similar to the human enzyme,  $\beta$ -glucocerebrosidase ( $\beta$ -D-glucosyl-N-acylsphingosine glucosylhydrolase, E.C. 3.2.1.45), a lysosomal glycoprotein enzyme, which catalyses the hydrolysis of the glycolipid glucocerebroside to glucose and ceramide. The amino acid sequence of the taliglucerase alfa has two extra amino acids (E and F) at the N-terminal and additional 7 amino acids at the C-terminal (DLLVDTM) flanking the core amino acid sequence of the human enzyme. These extra amino acids allow for specific targeting of Gaucher cells.

It was demonstrated in non-clinical studies that taliglucerase alfa uptake is specifically mediated by mannose receptors on macrophages and that, once in the macrophage, the enzyme is active on its substrate. Moreover, in the pivotal clinical trial (PB-06-001), efficacy of taliglucerase alfa for the treatment of Gaucher disease has been demonstrated.

To address the safety of taliglucerase alfa, Protalix performed single dose toxicity studies in the mouse and cynomolgus monkey, repeat dose studies (7, 14, and 29 days) in the marmoset monkey, repeat dose studies (28 days and 39 weeks) in the cynomolgus monkey, and Segment I and II reproductive toxicity studies in the rat and rabbit. Following single or repeated IV dosing, minimal to no systemic toxicity was observed. Effects were largely limited to the site of injection; the changes were related to the IV dosing technique and not to taliglucerase alfa. The drug did not adversely affect fertility and did not produce developmental malformations.

Taliglucerase alfa was evaluated for safety and pharmacokinetics in a Phase 1 study performed in six healthy subjects (P-01-2005) and for safety, efficacy and pharmacokinetics in a single pivotal, Phase 3 study performed in 32 patients with Gaucher disease (PB-06-001). The pivotal study was a multicenter, double blind, randomized, parallel group, dose ranging study in which

taliglucerase alfa was administered as an intravenous infusion every two weeks for 38 weeks (20 infusions). Patients were randomized to receive either 30 units/kg or 60 units/kg. Patients were enrolled in 11 centers around the world.

The primary efficacy analysis in study PB-06-001 demonstrated that taliglucerase alfa treatment significantly reduced spleen volume from screening to the Month 9 timepoint (taliglucerase alfa 30 units/kg, 26.91%; taliglucerase alfa 60 units/kg, 38.01%;  $p<0.0001$ ) and at the Month 6 timepoint (taliglucerase alfa 30 units/kg, 22.21%; taliglucerase alfa 60 units/kg, 29.94%;  $p<0.0001$ ) in patients with Gaucher disease.

The secondary efficacy analysis demonstrated that taliglucerase alfa treatment significantly increased hemoglobin level from the baseline at Month 9 timepoint (taliglucerase alfa 30 units/kg, 1.6 g/dL; taliglucerase alfa 60 units/kg, 2.2 g/dL;  $p<0.0001$ ). A significant reduction in liver volume from screening was also observed in both taliglucerase alfa dose groups at the end of the study (taliglucerase alfa 30 units/kg, 10.48%,  $P=0.0041$ ; taliglucerase alfa 60 units/kg, 11.11%,  $p<0.0001$ ). In addition, a significant increase in platelet count from baseline was observed in the 60 units/kg dose group at Month 9 ( $41,494/\text{mm}^3$ ,  $p=0.0031$ ) and a clinically relevant improvement in platelet count at Month 9 was also observed for the taliglucerase alfa 30 units/kg dose group ( $11,427/\text{mm}^3$ ,  $P=0.0460$ ). Improvements were also observed at the 6 month visit. At the end of study, all taliglucerase alfa treated patients had at least a 10% reduction in spleen volume.

Overall in PB-06-001, 23 taliglucerase alfa treated patients (30 units/kg, 12; 60 units/kg, 11) experienced 137 AEs (30 units/kg, 65; 60 units/kg, 72). Eight of these patients (30 units/kg, 3; 60 units/kg, 5) experienced 28 events (30 units/kg, 12; 60 units/kg, 16) which were considered by the investigator treatment related. All AEs were mild or moderate in intensity and the majority of the events resolved by the end of the study. No deaths or SAEs occurred during the study. Two patients (taliglucerase alfa 30 units/kg, 10-003; taliglucerase alfa 60 units/kg, 10-002) discontinued from the study due to a hypersensitivity reaction.

Adverse events judged to be related to treatment with taliglucerase alfa and occurring at an increased frequency were hypersensitivity, headache, and pruritis. These events occurred in a similar frequency in the 30 and 60 unit/kg dose groups. Other reported adverse events are abdominal pain, feeling hot, arthralgia, muscle spasms, dizziness, glycosuria and skin irritation.

A second clinical study (PB-06-002) has been initiated in patients with Gaucher disease and is ongoing. This study is an open label study in which patients previously treated with Cerezyme® (imiglucerase) are switched over to the same dose of taliglucerase alfa after establishing that their disease control is stable. Patients are being treated with taliglucerase alfa every 2 weeks for 9 months. Subjects aged 2 to < 18 years are eligible for enrolment in this study.

Study PB-06-003 is an extension study enrolling patients who have completed PB-06-001 and PB-06-002 and is ongoing. The patients continue to receive the same dose of taliglucerase alfa for an additional period of 15 or more months.

Study PB-06-004 is a treatment protocol enrolling patients who were previously treated with Cerezyme®, but who were put on a reduced dose regimen or discontinued because of a shortage of the drug. The protocol has been initiated and is ongoing.

## **5 STUDY OBJECTIVES**

The efficacy objectives of this trial are to assess the efficacy of taliglucerase alfa in subjects between 2 to < 18 years old with Gaucher disease, as measured by percent change in haemoglobin, chitotriosidase or CCL18, spleen and liver volume evaluated by MRI (or ultrasound), and platelet count, and change in growth and development (height, weight, Tanner Stage, bone age), bone disease, and Quality of Life from baseline.

The safety objectives are to assess the safety of taliglucerase alfa by clinical laboratory, physical examination, echocardiography, adverse events and anti-taliglucerase alfa antibodies

## **6 INVESTIGATIONAL PLAN**

### **6.1 Overall Study Design and Plan – Description**

This will be a multi-center, double-blind trial to assess the efficacy and safety of taliglucerase alfa in 10 untreated subjects between 2 to < 18 years old with Gaucher disease randomized to either 30 or 60 units/kg. Subjects will receive intravenous infusion of taliglucerase alfa every two weeks for 12 months. Subjects who tolerate the infusions well for three months will be eligible for home therapy based on approval of the investigator and the Medical Director. The total duration of treatment will be 12 months. At the end of the 12-month treatment period eligible subjects will be offered enrollment in an open-label extension study if taliglucerase alfa is not commercially available.

### **6.2 Discussion of Study Design and Choice of Control Group(s)**

This study represents one of the first pediatric exposures to taliglucerase alfa. Subjects will have a definitive diagnosis of Gaucher disease based on glucocerebrosidase activity with significant manifestations of the disease not previously treated with enzyme replacement therapy, or not treated in the last 12 months. This study presents an opportunity to assess the efficacy of taliglucerase alfa in a disease that does not improve spontaneously in this population. The parameters chosen as endpoints for this study are the most relevant parameters to the disease and allow a significant and relevant evaluation of improvement as a result of treatment for 12 months. Improvement in the clinical manifestations of the disease leads to the achievement of the therapeutic goals of Gaucher disease treatment in the medical community, which are enhanced quality of life and decreased risk for morbidities.

The study of two dose levels may provide clinically important information on whether there is a difference in treatment effect or a difference in rate of onset of treatment effect.

### **6.3 Selection of Study Population**

#### **6.3.1 Inclusion Criteria**

The subjects must meet the following inclusion criteria:

1. Male and female 2 years and <18 years old.
2. Diagnosis of Gaucher disease with leukocyte acid  $\beta$ -glucosidase activity  $\leq 30\%$  of the mean of the reference range for healthy subjects.
3. Subjects who have not received enzyme replacement therapy in the past or who have not received ERT in the past 12 months and have a negative anti-glucocerebrosidase assay assessment.
4. Subjects who have not received substrate reduction therapy (SRT) in the past 12 months.
5. Subjects whose clinical condition, in the opinion of the investigator, requires treatment with enzyme replacement therapy (ERT)

#### **6.3.2 Exclusion Criteria**

The presence of any of the following excludes a subject from study enrollment:

1. Subjects currently taking another investigational drug for any condition.
2. The presence of neurological signs and symptoms characteristic of Gaucher disease with complex neuronopathic features other than longstanding oculomotor gaze palsy.
3. Presence of unresolved anemia due to iron, folic acid, or vitamin B12 deficiency.
4. Previous hypersensitivity reaction to Cerezyme® (imiglucerase) or Ceredase® (alglucerase).
5. History of allergy to carrots.
6. The presence of HIV, HBsAg or hepatitis C infections.
7. The subject's parent(s) or legal guardian(s) are unable to understand the nature, scope and possible consequences of the study.
8. The presence of a medical, emotional, behavioral or psychological condition that, in the judgment of the Investigator, would interfere with the subject's compliance with the requirements of the study.

#### **6.3.3 Removal of Subjects from Therapy or Assessment**

Reasons for permanent discontinuation include the following:

- The subject experiences two or more Grade 3 toxicities or one or more Grade 4 toxicity considered by the investigator associated with taliglucerase alfa treatment (see Sections 8.2.4 Adverse Events and 13.5, Appendix 5 WHO Common Toxicity Criteria)

- Subjects who experience progressive hypersensitivity or severe hypersensitivity will be treated appropriately and withdrawn from the study (see Appendix 2 and Appendix 3)
- The subject requests to discontinue treatment
- Investigator feels that it is not in the best interest of the subject to continue treatment and/or if the investigator believes the subject can no longer be compliant with the requirements of the study.

For any discontinuation, the Investigator will obtain all the required details and document the date and the main reason for the premature termination. If the reason for discontinuation is an adverse event, the specific event or the main laboratory abnormality will be recorded in the CRF. The Investigator will make thorough efforts to document the outcome. The Investigator will attempt to continue to follow the subject for the full duration of the study or at least for 30 days following discontinuation. If circumstances prevent the subject from completing all visits, every attempt will be made to complete all procedures listed in Section 9 for Visit 28.

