| 
DURATION OF TREATMENT: 12 months
                                                                                                                                                                                                                                                                                                                                                                                                                                                                                                                                                                                                                                                                                                                                                                         |
| 
DISCONTINUATION FROM TREATMENT:
Reasons for permanent discontinuation include the following:
 
 
▪ The subject experiences two or more Grade 3 toxicities or one or more Grade 4 toxicity considered by the investigator associated with taliglucerase alfa treatment
 
▪ The subject who experiences progressive hypersensitivity or severe hypersensitivity are to be treated appropriately and withdrawn from the study
 
▪ The subject, or subject's parent or guardian, requests to discontinue treatment
 
▪ Investigator feels that it is not in the best interest of the subject to continue treatment and/or if the investigator believes that the subject can no longer be compliant with the requirements of the study
 
 |
| 
EFFICACY VARIABLES:
 
 
▪ The primary efficacy variable is median percentage and the interquartile range for change from baseline in haemoglobin
 
▪ Secondary efficacy variables are: 
 
○ Percent change from baseline in chitotriosidase or CCL18
 
○ Percent change from baseline in spleen and liver volume
 
○ Percent change from baseline in platelet count
 
 
 
                                                                                                                                                                                                                                                                                                                   |

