| Echocardiography                        |                      | X                   |                                                     |                    |                                 |                     |                             |                     |                                 | X        |
| Left Hand and wrist X-ray evaluation    |                      | X                   |                                                     |                    |                                 |                     |                             |                     |                                 | X        |
| Quality of Life (CHQ PF-28)             |                      | X                   |                                                     |                    |                                 | X                   |                             |                     |                                 | X        |
| Chitotriosidase or CCL18 biomarker      |                      | X                   |                                                     | X                  |                                 | X                   |                             | X                   |                                 | X        |
| Mutation analysis                       |                      | X                   |                                                     |                    |                                 |                     |                             |                     |                                 |          |
| DEXA                                    |                      | X                   |                                                     |                    |                                 |                     |                             |                     |                                 | X        |
| IV Infusion (ERT)                       |                      | X                   | X                                                   | X                  | X                               | X                   | X                           | X                   | X                               | X        |

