9. DEXA
10. Taliglucerase alfa infusion

Perform the following procedures for taliglucerase alfa dosing:

- Observe the subject clinically for a minimum of 1 hour after dosing
- Evaluate vital signs every 30 minutes
- Evaluate the injection site.

Protocol Number PB-06-005

Protalix Ltd.  
April 28, 2010

---

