#### **Treatment algorithm**

With the onset of any of the above clinical signs, immediately discontinue study medication administration and initiate the following monitoring.

- Continuous electrocardiographic monitoring
- Continuous pulse oximetry
- Measure blood pressure every 5 minutes
- Perform chest auscultation every 5 minutes

- 
- Blood samples need to be collected for Tryptase (29-33) and antibodies. Tryptase samples need to be withdrawn at:
    - 1st sample taken 0.25-3 hours after onset of symptoms
    - 2nd sample taken between 3-6 hours
    - 3rd sample taken 24-48 hours to verify the return to baseline.

In the case of progressive or severe hypersensitivity, treat appropriately and withdraw the subject from the study.

Treat as follows:

Urticaria or edema of the face, neck, or soft tissues

- Epinephrine 1:1000 solution, 0.5 mL subcutaneously, repeat as needed every 5-10 minutes
- Antihistamines
- Corticosteroids

Hypotension (systolic blood pressure (SBP)  $\leq$  90 mmHg)

- Isotonic sodium chloride solution, 1 L every 30 minutes as needed to maintain SBP > 90 mmHg
- Epinephrine 1:10,000 solution given IV at 1 µg/minute initially, then 2-10 µg/minute to maintain SBP > 90 mmHg
- Norepinephrine 4 mg in 1 L 5% dextrose in water given IV at 2-12 µg/min to maintain SBP > 90 mmHg
- Glucagon 1 mg in 1 L 5% dextrose in water give IV at 5-15 µg/minute for refractory hypotension

Bronchospasm

- Oxygen by face mask at 6-8 L/minute to maintain oxygen saturation at > 90%
- Epinephrine 1:1000 solution, 0.5 mL subcutaneously
- Albuterol 0.5 mL of 0.5% solution in 2.5 mL of sterile saline every 15 minutes up to three doses
- Inhaled beta-agonists
- Corticosteroids

Laryngeal edema

- Epinephrine 1:1000 solution, 0.5 mL subcutaneously, repeat as needed every 5 to 10 minutes
- Corticosteroids

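### Section 6.3.3 asks for every Visit 28 procedure after a discontinuation and does not except the taliglucerase alfa infusion (minor internal inconsistency with a safety implication)

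*Protocol*

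**What the plan says.** Protocol Section 6.3.3 gives four grounds for permanent discontinuation: drug-associated toxicity (two or more Grade 3 events, or at least one Grade 4), progressive or severe hypersensitivity, the subject's request, and the investigator's judgement of best interest or compliance. The synopsis carries a matching list under the heading "DISCONTINUATION FROM TREATMENT".

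The last paragraph of Section 6.3.3 applies to discontinuation for any reason. The investigator documents the reason and outcome and tries to follow the subject to the end of the study, or for at least 30 days. It closes with a fallback: "If circumstances prevent the subject from completing all visits, every attempt will be made to complete all procedures listed in Section 9 for Visit 28".

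Section 9.2.10 sets out Visit 28 (Month 12) as ten numbered items. The last is "10. Taliglucerase alfa infusion", followed by the dosing procedures: observation, vital signs and injection-site check. The intravenous infusion row of the flow chart in Section 9.1 is marked at Visit 28 with no condition or footnote.

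Appendix 3 (Section 13.3) states: "In the case of progressive or severe hypersensitivity, treat appropriately and withdraw the subject from the study".

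**The concern.** The fallback sentence points to a complete list, and that list contains a dose of study drug. A subject whom the protocol has just taken off the drug for good is, on the literal text, among those for whom every attempt is to be made to complete that list.

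For a subject who stops by request or for poor compliance, this is untidy. For a child stopped for drug-associated Grade 3 or 4 toxicity, or for progressive or severe hypersensitivity, the item swept in is re-exposure to the drug held responsible. A safety stopping rule should not depend on the reader working out that one listed procedure is meant to be skipped. What is at stake is the clarity of that rule, not the analysis.

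**Working it through.** The protocol gives no figure on this point and no calculation decides it. The check is to follow the cross-reference and compare the texts.

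1. **Who is covered.** The closing paragraph of Section 6.3.3 covers discontinuation for any reason, so it includes the toxicity and hypersensitivity cases listed just above it.
2. **When the sentence applies.** It applies when the subject cannot complete all visits.
3. **What it asks for.** It says "every attempt will be made to complete all procedures listed in Section 9 for Visit 28". No exception is stated.
4. **What the list contains.** Section 9.2.10 has items 1 to 10. Items 1 to 9 are adverse events and concomitant medications, examination, laboratory tests, quality of life, echocardiography, organ volumes, Tanner stage, bone age and DEXA. Item 10 is the infusion. So 1 of 10 numbered items is dosing, and the dosing procedures below the list depend on it.
5. **Whether another text removes item 10.** Section 9.2.10 has no condition for discontinued subjects. The flow chart has none on its infusion row. There is no separate early-termination visit with its own list. Calling the list assessments does not help, because Section 9.2.10 introduces all ten items, infusion included, as assessments.
6. **What it conflicts with.** Section 6.3.3 calls these discontinuations permanent, the synopsis describes them as discontinuation from treatment, and Appendix 3 orders withdrawal after a progressive or severe reaction. Appendix 3 allows premedication for later infusions only after early signs, or after rash or urticaria that responds promptly to oral antihistamine. It offers no route to another dose after a progressive or severe reaction.

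Steps 1 to 5 give a literal request that includes a dose, and step 6 gives rules that exclude one. The two cannot both be followed as written.

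**Background only.** Section 4 reports that in the pivotal study of 32 patients (PB-06-001), two "discontinued from the study due to a hypersensitivity reaction": 2/32 = 6.25%. If that per-subject rate carried over, 10 × 0.0625 = 0.625 such discontinuations would be expected among 10 subjects. So the situation can arise in this trial. The figure says no more than that:

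- The pivotal study treated for 38 weeks, against 12 months here.
- Section 4 says all adverse events in that study were mild or moderate and none was serious. That scale is not the Appendix 3 classification, but it weakens 2/32 as a guide to progressive or severe reactions.
- The sentence also requires that the subject cannot complete all visits, and the protocol gives no rate for that.

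**The case against.** The strongest reply is that the protocol already settles the matter. The section concerns removal from therapy, the discontinuation is permanent, and Appendix 3 requires withdrawal. A specific stopping rule overrides a general sentence about collecting end-of-study data. The rest of the paragraph deals only with documentation and follow-up.

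Strict literalism also proves too much. Every visit from Visit 1 to Visit 28 carries an infusion, so following a stopped subject through the remaining visits would, on the same reading, mean continued fortnightly dosing. Nobody would read it so. The sentence is also soft: it asks for attempts and orders no dose.

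Most of this stands. It shows that redosing is not intended and makes it unlikely, and it limits the point to minor. It does not make the sentence correct. The sentence is an operative instruction whose literal result is wrong in a safety setting. The remark about the other visits is a reason to put the clarification in the flow chart as well as in Section 6.3.3.

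A reader might go further and infer that the protocol directs investigators to re-challenge children after a severe reaction, or that 2 of 32 measures the chance of this happening. The documents support neither. The stopping and withdrawal rules point the other way, and the pivotal-study figure measures neither how often the Visit 28 fallback would apply nor the chance of a dose being given.

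**Conclusion.** The point holds as a minor internal inconsistency with a safety implication. Section 6.3.3, followed exactly as written, includes a study drug infusion among the procedures sought after discontinuation, and this conflicts with permanent discontinuation and with withdrawal after progressive or severe hypersensitivity.

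Its size is one item of ten in a cross-referenced list. It does not affect the haemoglobin endpoint, any secondary endpoint, the sample size or any estimate. No design decision is in question. The conclusion rests on the text alone and needs no assumption about event rates. The probability of an unintended dose cannot be derived from the protocol and is expected to be low.

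**What to change.** In Section 6.3.3, replace the request for every Visit 28 procedure with: *all Visit 28 assessments (items 1-9), excluding the taliglucerase alfa infusion and its dosing procedures*. The infusion has to be named, because Section 9.2.10 counts it among the assessments.

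In Section 9.1, add a footnote to the intravenous infusion row: *no infusion is given at any visit after permanent discontinuation*. This also covers subjects who stop treatment but continue to attend visits.

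The cost is one phrase and one footnote. Visit schedule, follow-up, adverse event collection and the withdrawal wording stay as they are, and no data are lost.
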